#### Composition of the data monitoring committee, its role and reporting structure

A study nurse of the University Hospital of Basel will be responsible for study monitoring. Monitoring visits at the investigator’s site are planned according to the pre-defined monitoring plan approved by the local ethics committee. Monitoring will commence with a trial initiation visit (TIV), followed by regular monitoring visits within time frames that will have to be determined according to recruitment progress. Monitoring visits will be documented, and information stored within the ISF. Monitoring will be independent from sponsor and competing interests.

The source data/documents are accessible to monitors, the competent ethics committee and other involved competent authorities, and questions are answered during possible monitoring.

#### Adverse event reporting and harms

Since the utilised enteral nutrition is the standard formula for the initial phase in ICU patients at the University Hospital Basel, no severe adverse events relating to the components of this formula are expected after careful enrolment following the specified exclusion criteria. All study patients will be monitored with respect to any possible adverse events related to the administration of enteral nutrition. An accountability log for the nutrition formula will be provided for each patient with the batch number of the administered bags.

Fresubin© Intensive comes under risk category A in our trial. It is a medicinal product authorised in Switzerland, and its use in this study is in accordance with the prescribing information: critically ill ICU patients with increased need for protein. Possible side effects of intermittent feeding in the intervention group are expected to be similar to the familiar side effects (e.g. meteorism, diarrhoea and constipation) of continuous feeding. The aspiration risk will be limited due to frequent controls of GRV after every feeding cycle. The enteral feeding will be stopped immediately in case any adverse events, including GRV > 300 ml, vomiting, regurgitation or aspiration, occur. Feeding will be restarted at the next planned cycle at the highest dose previously tolerated. If a patient of the experimental group does not tolerate the administered dose of nutrition over three consecutive feeding cycles (despite common prokinetics as 100 mg erythromycin and 10 mg metoclopramide, whenever no contraindication is applicable), he or she will be crossed-over to the standard continuous feeding group. If a patient of the CF group does not tolerate the administered dose of nutrition over three consecutive cycles, the treating physician will discuss how to proceed together with the study team.

For monitoring of hypo/hyperglycaemia, we will determine the blood glucose with an interval of 3 h maximum and if applicable administer insulin according to our standardised ICU protocol considering the state of health and presence of diabetes mellitus.

The study will be carried out in accordance with the protocol and with policies detailed in the current version of the Declaration of Helsinki, the guidelines of Good Clinical Practice (GCP) issued by International Conference on Harmonisation of Technical Requirements for Registration of Pharmaceuticals for Human Use (ICH), Swiss law and Swiss regulatory authority’s requirements. The competent ethics committee (CEC) and regulatory authorities will receive annual safety and interim reports and will be informed about study stop/termination in agreement with local requirements.

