The administration of intermittent feeding (IF) versus continuous feeding (CF) is a topic of ongoing controversy [1, 16–24]. The possible benefits of IF have overcome concerns of adverse effects such as pulmonary aspiration and have blazed a trail for further investigations challenging the definition of continuous feeding as the standard for ICU patients [21, 25]. Insulin plays an essential role in MPS in the presence of amino acids and importantly blunts muscle protein breakdown [26]. Earlier investigations reported that MPS could only be stimulated for a limited time in healthy individuals, despite sufficient availability of amino acids [27]. Another study in healthy men revealed that plasma insulin concentrations increased significantly to a maximum of + 303% for 60 min after application of an oral protein bolus and then decreased after 90 min [8]. Moreover, in 2015, Hooper and Marik suggested in their reviews based on the findings of trials in humans and animals that enteral nutrition given continuously would even reduce protein synthesis [1, 11].

In addition, compared to continuous feeding, IF is assumed to have direct potential advantages over gastrointestinal-hormone secretion [21, 28] and indirect advantages due to preservation of pancreatic and gallbladder function [21], elevated insulin secretion [28, 29] and improvement of glucose control [1]. However, whether this physiologic hormone pattern translates into molecular muscle anabolism remains unknown.

In this study, we hypothesise that target quantity of protein is reached earlier (within 36 h) with enteral IF compared to standard CF. In addition, we expect IF to be equally well tolerated, incidence of adverse events to be similar between groups and MPS to be higher in the experimental group.

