**Day 2**													
Protein dose^1^	0.4			0.4			0.4			0.4			
Flow rate^2^	200–360			200–360			200–360			200–360			
Total protein^3^	1.4			1.6			1.6			1.6			

*GRV* gastric residual volume

^1^[g/kgBW/30 min], 4 nutrition cycles/24 h: each with 30 min nutrition followed by a 4-h break and 30 min GRV measure, night time break of 4 h. Total time of feeding, 2 h; GRV measurements, 2 h; break, 20 h

^2^[ml Fresubin© Intensive/30 min], depending on bodyweight

^3^Total of administered protein of the preceding 24 h [g/kgBW]

**Table 2 Tab2:** Continuous feeding protocol (control group)

Time	06:00–11:00	11:00–12:00	12:00–17:00	17:00–18:00	18:00–23:00	23:00–00:00	00:00–05:00	05:00–06:00
	Nutrition	Break + GRV	Nutrition	Break + GRV	Nutrition	Break + GRV	Nutrition	Break + GRV

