##### Datasets to be analysed, analysis populations

An intention-to-treat and per protocol analysis of ICU patients who meet all inclusion and no exclusion criteria will be performed.

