### Outcomes

Based on evidence that intermittently fed patients may reach their protein target faster than continuously fed patients, we chose to evaluate the time (in hours) until patients reach the protein target of 1.5 g protein/kg BW/24 h to be able to calculate a significant reduction and thereby verify our hypothesis. Secondary outcomes will be used to compare tolerance of each enteral feeding regimen.

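### After a switch that is automatic in the intermittent arm only, continuous-feeding cycles count as intermittent-feeding tolerance, and the switch trigger itself is not compared between arms

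*Protocol article*

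**What the plan says.** The section on adverse event reporting and harms sets one trigger with two consequences. If an IF patient "does not tolerate the administered dose of nutrition over three consecutive feeding cycles", despite prokinetics where these are not contraindicated, then "he or she will be crossed-over to the standard continuous feeding group". If a CF patient reaches the same point, "the treating physician will discuss how to proceed together with the study team".

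The switch is not among the listed reasons for withdrawal (Criteria for discontinuing or modifying allocated interventions), so a switched patient ordinarily stays in the study. The analysis sets are given in one sentence: "An intention-to-treat and per protocol analysis of ICU patients who meet all inclusion and no exclusion criteria will be performed".

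The secondary outcome measures include gastric residual volume after each cycle and counts of gastrointestinal and aspiration events per feeding cycle. Their purpose is stated in the Discussion: "Secondary outcomes will be used to compare tolerance of each enteral feeding regimen". The expected result is in the Background: "we expect IF to be equally well tolerated, incidence of adverse events to be similar between groups". Reaching the three-cycle trigger is not on the outcome list for either arm.

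**The concern.** The tolerance question is about regimens, but after a switch the IF arm no longer delivers its regimen in the patients who failed it. Their later cycles are continuous feeding, yet as randomised they enter the IF totals. The CF arm has no matching automatic change. Dilution of this kind is usually called conservative because it works against finding a difference. Here the expected tolerance result is similarity, so dilution would work towards the expected answer.

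Reaching the point where the allocated regimen is judged not tolerated is a direct measure of tolerance. The protocol defines that point for both arms but does not compare it. A reader could therefore see similar event rates without learning how many patients in each arm got there.

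**Working it through.** **Inputs from the protocol article**
- Cycles per day: 4 (footnote to Table 1, "4 nutrition cycles/24 h: each with 30 min nutrition followed by a 4-h break").
- Study period: 7 days, so T = 4 x 7 = 28 cycles. The minimum follow-up used in the sample size section is 5 days, so T = 4 x 5 = 20 cycles.
- Patients per arm: 30, so a full IF arm has 30 x 28 = 840 cycles.
- Trigger: 3 consecutive non-tolerated cycles, so the earliest possible switch is after cycle 3.

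**Assumptions (not in the document)**
- p, the share of IF patients who switch: 10% and 20%.
- c, the last cycle before the switch: 5 as the worked case (cycles 3-5 not tolerated), with 3, 8 and 20 for range.

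The protocol states no expected number or timing of switches, so there is no planned figure to reproduce.

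**Formulas**
- Share of a switched patient's cycles given as continuous feeding: (T - c)/T.
- Share of all IF-arm cycles: p x (T - c)/T.

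| T | c | (T - c)/T | p = 10% | p = 20% |
|---|---|---|---|---|
| 28 | 3 | 25/28 = 89% | 8.9% | 17.9% |
| 28 | 5 | 23/28 = 82% | 8.2% | 16.4% |
| 28 | 8 | 20/28 = 71% | 7.1% | 14.3% |
| 28 | 20 | 8/28 = 29% | 2.9% | 5.7% |
| 20 | 5 | 15/20 = 75% | 7.5% | 15.0% |

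In counts for the worked case: 3 patients x 23 = 69 of 840 cycles, and 6 patients x 23 = 138 of 840 cycles.

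**What this could do to an event rate (all rates assumed)**

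Take p = 20% and c = 5. Tolerating patients have 0.10 events per cycle. Non-tolerating patients have one event in each of cycles 3-5 and none in cycles 1-2.
- If they would go on at 0.50 per cycle on IF: (3 + 23 x 0.50)/28 = 0.518, so the arm rate is 0.8 x 0.10 + 0.2 x 0.518 = 0.184.
- If they fall to 0.10 after the switch: (3 + 23 x 0.10)/28 = 0.189, so the arm rate is 0.8 x 0.10 + 0.2 x 0.189 = 0.118.
- If they stay at 0.50 after the switch, the arm rate remains 0.184 and nothing is blurred.

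The effect therefore depends entirely on how switched patients fare on continuous feeding.

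**The case against.** The strongest reply is that analysing switched patients as randomised is what intention-to-treat means. It compares a strategy, IF with a fallback to the standard regimen, and that is a legitimate comparison. CF is the current standard, so some asymmetry in conduct is structural. This stands, and it is why the as-randomised analysis should be kept. But the Discussion says the outcomes compare the tolerance of each regimen, and the strategy comparison alone does not answer that.

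Other points stand in part:
- Early switches may be uncommon. After an event, feeding restarts at the highest dose already tolerated, so a patient failing at cycle 3 needs two more failures at or below a tolerated dose. The worked case is close to the earliest possible, and 82% describes one such patient, not the arm.
- The analysis section plans comparisons at each time point for the secondary outcomes, so cycles before any switch can be compared undiluted. Later time points cannot.
- The component events are recorded per cycle in both arms, so intolerance is not ignored. What is missing is the comparison of the trigger.

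Two stronger readings are tempting and not supported:
- A reader might infer that the per-protocol set drops IF non-tolerators and keeps CF ones. The set is not defined in the article, and its definition may be in an analysis plan not shown. A patient switched under a protocol rule could count as adherent, and a CF non-tolerator could be withdrawn on the physician's demand.
- A reader might infer that every planned analysis favours IF. For the primary superiority aim, moving IF patients onto continuous feeding would tend to make the arms more alike.

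**Conclusion.** The concern holds for the tolerance comparison. As written, continuous-feeding cycles given after a switch count as IF tolerance, and the trigger that would show the difference most directly is not compared.

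The size is unknown because the number and timing of switches are not given. At an assumed 10-20% of IF patients switching after cycle 5, about 8-16% of IF-arm cycles over 7 days are affected; later switches affect fewer. The blurring towards similarity requires that switched patients tolerate continuous feeding better, which the document does not show. No bias in a known direction is established for the primary outcome, and the per-protocol point is conditional on how that set is defined.

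This is a cheap improvement that lets the trial answer its own tolerance question. It is not a defect that invalidates the plan.

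**What to change.** 1. Record reaching three consecutive non-tolerated cycles in the same way in both arms, and compare it as randomised as a tolerance outcome.
2. Keep the as-randomised analysis of gastric residual volume and events. Add a supporting analysis of cycles up to the trigger in both arms. State that follow-up in this analysis is cut by intolerance itself, so it supplements the main comparison and does not replace it.
3. If the per-protocol set would exclude patients for meeting the trigger or for switching, apply the same trigger-based rule in both arms: keep such patients in both or remove them from both.

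Clinical management after the trigger need not change, and no view is taken on it here. The cost is protocol and analysis-plan wording plus a little extra analysis; the bedside protocol already has space to document events in every cycle. The other possible downside is a less favourable tolerance result for IF.

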##### Adverse events

According to the Swiss regulations for clinical trials in human research, it is not mandatory for clinical trials in risk category A to document adverse events. For safety reasons, side effects of enteral feeding as mentioned in the secondary outcomes will be documented during the course of this study.

##### Serious adverse events

Many ICU patients suffer from various adverse events that are life-threatening and/or prolong existing hospitalisation. Therefore, we will only document and report pulmonary aspiration (defined as evidence of nutrition formula within the tracheo-bronchial branches) or death of patients as SAE.

The occurrence of abovementioned SAEs will be assessed during every ICU shift. The sponsor must report all changes in research activity and unanticipated problems to the responsible ethics committee. Likewise, all SAEs must be reported within 7 days if fatal, otherwise within 15 days. The sponsor will provide an annual safety report.

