##### Exclusion criteria

*Start of enteral nutrition before ICU admission or study inclusion*. To provide the same baseline, patients will only be included whenever they did not receive enteral nutrition before study inclusion.

*Pregnant or breast feeding women*. A negative pregnancy test (i.e. beta-hCG in urine or serum) will be necessary prior to study inclusion in women aged < 45 years.

*Clinically significant acute or chronic kidney failure with GFR < 20 ml/min.* Schwartz et al. [34] concluded that although significant restrictions in protein intake may not be necessary for critically ill patients with acute kidney injury, excessive protein provision in these patients could have a negative effect on renal function and lead to azotaemia. For safety reasons, the GFR value is intentionally set low to exclude patients with severely restricted kidney function.

*BMI ≤ 18 or ≥ 35 kg/m*^*2*^. Patients with underweight or obesity will be excluded from the trial because of altered muscle mass, pre-existing endocrine dysfunction or diverging energy or protein requirements.

*Intestinal perforation, peritonitis, intestinal fistula, necrosis or other contraindication to enteral nutrition.* Gastrointestinal conditions will be excluded to prevent adverse effects of enteral feeding and to decrease the number of patients not completing the study protocol.

*Noradrenaline ≥ 0.5 μg/kg BW/min.* Noradrenaline leads to decreased blood circulation in the muscles. Therefore, analysis of muscle biopsies might be biassed and incision healing negatively affected due to local decrease in blood circulation.

*Inherited and chronic skeletal muscle disorder (e.g. motor neuron disease).* Because of altered muscle metabolism and lower total muscle mass, the analysis of muscle biopsies might be biassed if these patients are included in the study.

*Paralysis (e.g. hemiplegia, tetraplegia and paraplegia).* Because of altered muscle metabolism and lower total muscle mass.

*Immunosuppression (e.g. due to underlying disease or drug regime)*. Patients with immunosuppression suffer from increased risk of infection due to muscle biopsy. Additionally, corticosteroids are known for their influence on muscle breakdown.

*Haematologic malignancy.* Haematologic malignancies might negatively affect blood coagulation and lead to increased bleeding after muscle biopsy.

*Severe coagulopathy at time of inclusion.* Because of increased intramuscular bleeding and haematoma after the muscle biopsy.

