#### Strategies to improve adherence to interventions

To improve adherence to intervention protocols and monitoring adherence, all study patients receive a bedside protocol with the study group, feeding cycles and calculated amount of nutrition, space for documentation of adverse events within every nutrition cycle. The study team fulfils daily controls and if needed reminds bedside nurses to document all the values needed for the study.

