**Fig. 1 Fig1:**
[figure not shown]
Study Flow Chart

**Table 3 Tab3:** Study schedule

	Screening	Allocation	Observation time					Closeout
Time	t_−1_	t_0_	t_1_	t_2_	t_3_	t_4_	t_5_	t_6_
Day	0	1	2	3	4	5	6	7
Eligibility criteria	x							
Informed consent	x							
Randomisation	x							
Baseline data	x							
Muscle biopsy and ultrasound	x^1^							x
Start feeding		x^2^						
Vital parameters	x	x	x	x	x	x	x	x
Primary variables		x	x	x	x	x	x	x
Secondary variables^3^	x	x	x	x	x	x	x	x
SAEs		x	x	x	x	x	x	x

^1^Performance of muscle ultrasound and biopsy on inclusion day until 3:00 pm will allow enteral feeding starting the next day at 6:00 am. Whenever the study team is not able to perform both before 3:00 pm, these study procedures will be postponed to the next day and study feeding will start the day after at 6:00 am

^2^6:00 am

^3^Including laboratory parameters, documentation of side effects of enteral feeding and assessment of SOFA score

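### The protocol names bleeding, haematoma, infection and poor incision healing as biopsy risks, but its event-recording rules include no systematic record of biopsy complications

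*Protocol article*

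**What the plan says.** **Risks named.** In the Protocol article, the explanatory list under Exclusion criteria justifies several exclusions by harm from the biopsy. Severe coagulopathy is excluded "Because of increased intramuscular bleeding and haematoma after the muscle biopsy". On immunosuppression it says "Patients with immunosuppression suffer from increased risk of infection due to muscle biopsy". Haematologic malignancy is excluded for bleeding after the biopsy, and high-dose noradrenaline partly because the incision may heal poorly.

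**Events recorded.** The section Serious adverse events sets a closed list: "we will only document and report pulmonary aspiration", which it defines as formula found in the airways, or death. The section Adverse events adds that "side effects of enteral feeding as mentioned in the secondary outcomes will be documented during the course of this study". The list it points to, under Secondary outcome measures, holds gastrointestinal events and aspiration. The opening of Adverse event reporting and harms is framed the same way: "All study patients will be monitored with respect to any possible adverse events related to the administration of enteral nutrition". The bedside form gives "space for documentation of adverse events within every nutrition cycle".

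**Timing.** Table 3 puts the first biopsy at t−1 and the second at t6. The SAE row is empty at t−1 and marked from t0 to t6. Footnote 1 to the table reads "Performance of muscle ultrasound and biopsy on inclusion day until 3:00 pm will allow enteral feeding starting the next day at 6:00 am". Participant timeline sets closeout at the end of day 7, or on the day of ICU discharge if that is earlier.

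**The concern.** The biopsy serves the research question and is not part of feeding. It is planned in patients who may be included on an independent physician's declaration because they cannot consent themselves. The protocol treats its complications as serious enough to exclude several groups, yet does not provide for counting them in the patients who are enrolled.

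Two things are at stake. The trial would have no reliable complication rate to report for a procedure it performs up to twice per patient. In addition, the annual safety report and the safety ground for early termination would have no systematically collected biopsy information behind them.

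This is not detail that a condensed article leaves to a fuller document. The word restricting the SAE list, and the Table 3 row, positively fix a scope and a window.

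**Working it through.** No sample size, error rate or event rate underlies this point, so the check compares the sections with one another.

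**1. Scope.** Harms named for the biopsy, compared with what is recorded:

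| Harm named under Exclusion criteria | On the SAE list? | Among the feeding side effects under Secondary outcome measures? |
|---|---|---|
| Bleeding or haematoma | No, unless fatal | No |
| Infection | No, unless fatal | No |
| Impaired incision healing | No | No |

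Monitoring is unlikely to fill the gap. Under Frequency and plans for auditing trial conduct, monitors check recorded events against the protocol's own definition.

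**2. Start of the window.** The first biopsy is at t−1. The SAE row starts at t0, which its own subsection heading describes as the day after biopsy and ultrasound. For a biopsy done on the inclusion day by 3:00 pm, with feeding at 6:00 am, the interval is 9 h to midnight plus 6 h, or at least 15 h, if recording starts with feeding. If day 1 is counted from midnight, it is at least 9 h. If the biopsy is postponed by a day, feeding start and t0 move with it, so the biopsy day remains uncovered.

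**3. End of the window.** The repeat biopsy is on day 7, or on the day of discharge if the patient leaves on day 5 or 6. Closeout falls on the same day. At most the rest of that day is covered. Provisions for post-trial care sets study follow-up to hospital discharge only for participants with aspiration. A wound infection that appears days later falls outside any planned record.

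**4. Order of the two defects.** Scope comes first. Under the current list, opening the window earlier would capture no non-fatal biopsy complication. The window matters once the list is widened.

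**5. Number of biopsies.** Two biopsies in each of 60 patients gives 60 × 2 = 120, but this is illustrative and not a ceiling. Refusals, allowed in the missing-data section, lower the count. Replacement of patients who leave on days 1–4, some already biopsied, raises it. To illustrate what a record could offer, zero events in exactly 60 biopsied patients would give a one-sided 95% upper bound of 1 − 0.05^(1/60) = 4.9% per patient. The conclusion rests on neither figure.

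**The case against.** The short list is a reasoned choice. Adverse events says that recording is not mandatory in risk category A. Serious adverse events explains that ICU patients have many life-threatening events anyway. Ethics approval was given. Biopsy risk is handled by exclusion and by operator training. Both arms have the same biopsies, so the primary outcome and the between-arm comparisons are unaffected.

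Most of this is true, but it does not meet the point. The article assigns category A to the feeding formula and does not say how the biopsy is classed. Background illness is a good reason not to report every life-threatening event, but a weak one for omitting a local complication at a known puncture site. Exclusion lowers the risk without measuring what remains.

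A reader might go further and infer that a biopsy complication could never enter the data, or that the trial could not detect a biopsy problem. The documents do not support that:

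- A fatal complication on days 1–7 would be recorded as a death.
- The safety ground for termination under Interim analyses, and withdrawal by the treating physician or study team, are not tied to the SAE list.
- All participants stay under ICU monitoring.
- Unanticipated problems must go to the ethics committee. This helps little for bleeding and infection, which the protocol anticipates.

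A reader might also infer that biopsies are imposed without choice. The missing-data section says that patients and next of kin may take part while declining them.

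**Conclusion.** The point holds as a gap in safety recording. Followed as written, the protocol yields no planned, systematic record of biopsy complications, so no reliable rate can be reported and safety review has no systematic biopsy data. It does not follow that a problem could not be noticed or acted on.

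The effect is on knowledge of patient safety. It does not bias the treatment comparison. The change should be made, but the point does not threaten the trial's main conclusion.

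The verdict assumes that the eCRF and any fuller protocol follow the closed list in the article. If biopsy-site events are already recorded there, the article needs only to say so.

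**What to change.** Reconcile the explanatory list under Exclusion criteria, Table 3, Adverse events and Serious adverse events:

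1. Add to the eCRF event list the biopsy-site harms the protocol already names: bleeding, haematoma, infection and impaired incision healing.
2. In Table 3, start recording of these events at the first biopsy (t−1).
3. Carry the recording past the repeat biopsy to discharge, using existing ICU or hospital records, as is already planned to hospital discharge for aspiration.
4. Report those that are serious as SAEs.
5. Report the results against the number of biopsies actually taken. State how this fits with the rule that destroys the data of patients who leave on days 1–4, since some of them will have had the baseline biopsy.

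The cost is a few eCRF fields, a change to Table 3 and a small extra documentation load for staff who already assess SAEs every shift. No feeding rule or study procedure changes.

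### New non-fatal intestinal perforation, peritonitis or necrosis under study feeding is not a defined trial event, so it would not be counted by arm

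*Protocol article*

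**What the plan says.** All places are in the protocol article.

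- **Serious adverse events.** Because life-threatening events are common in ICU patients, "we will only document and report pulmonary aspiration (defined as evidence of nutrition formula within the tracheo-bronchial branches) or death of patients as SAE". Fatal SAEs are to be reported within 7 days and others within 15.
- **Adverse events.** Risk category A does not oblige the trial to document adverse events. For safety reasons the protocol nevertheless says that "side effects of enteral feeding as mentioned in the secondary outcomes will be documented during the course of this study".
- **Secondary outcome measures.** The events named are vomiting, regurgitation, nausea, meteorism, diarrhoea, constipation and pulmonary aspiration. Gastric residual volume and regurgitated volume are also measured.
- **Adverse event reporting and harms.** This section is wider: "All study patients will be monitored with respect to any possible adverse events related to the administration of enteral nutrition".
- **Exclusion criteria.** One criterion reads "Intestinal perforation, peritonitis, intestinal fistula, necrosis or other contraindication to enteral nutrition". The explanation under Definition/conditions begins "Gastrointestinal conditions will be excluded to prevent adverse effects of enteral feeding". It adds a second reason: fewer patients failing to complete the protocol.
- **Background and rationale.** The investigators expect the incidence of adverse events to be similar in the two groups.

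**The concern.** The general monitoring promise covers any adverse event related to enteral feeding, but the recording rules cover two short lists. The serious gut conditions that bar a patient from entering are in neither list once feeding has begun.

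The two arms differ mainly in how fast the formula enters the stomach. At full dose, Table 1 gives 200–360 ml in 30 min and Table 2 gives 40–72 ml per hour. As hourly rates these are 400–720 ml/h and 40–72 ml/h, a ten-fold difference. Gut tolerance is therefore central to what is compared, and the protocol states an expectation about it.

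At stake is whether the trial's account of harms by arm can speak to serious intestinal events at all. Under the stated rules, a reader of the results could not tell whether such events were absent or simply not collected. Early termination for safety and the annual safety reports also depend on what is recorded.

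**Working it through.** The protocol states no figure on this point, so there is none to reproduce. The check compares the text, with some arithmetic for scale.

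**1. Where a new non-fatal perforation, peritonitis or intestinal necrosis could be recorded**

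| Route (section) | Covers it? | Count by arm? |
|---|---|---|
| SAE record (Serious adverse events) | No: aspiration and death only | No |
| Side-effect record (Adverse events, with Secondary outcome measures) | No: not on the list | No |
| Follow-up to hospital discharge (Provisions for post-trial care) | No: only for patients who aspirate, and for complications of aspiration | No |
| Bedside sheet (Strategies to improve adherence): "space for documentation of adverse events within every nutrition cycle" | Possibly: no event types are named | No defined category |
| Ethics committee (Serious adverse events): "The sponsor must report all changes in research activity and unanticipated problems to the responsible ethics committee" | Possibly: depends on someone judging it unanticipated | No |
| Monitoring visits (Frequency and plans for auditing) | Events are checked for consistency with the protocol's definition, which omits these | No |

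The two defined lists exclude the event. The informal routes may catch a case but have no definition, no set ascertainment and no tabulation. A fatal case is a death under the SAE rule, but its intestinal cause is not a defined item.

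**2. What happens after withdrawal**

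The discontinuation criteria allow withdrawal for safety. Under Plans to promote participant retention, withdrawal on days 1–4 leads to destruction of all data and replacement of the patient. A patient withdrawn in that window because of a gut complication could therefore lose even an informal note in the study data.

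**3. Scale**

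The number per arm is 30, 60 in total (Data management, Sample size). The documents give no event rate, so the rates below are assumptions.

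*Bound from zero events in one arm, if every event were recorded:*
- One-sided 95%: 1 − 0.05^(1/30) = 0.095, or 9.5%.
- Two-sided exact 95%: 1 − 0.025^(1/30) = 0.116, or 11.6%.

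*Chance of at least one case among 60 patients, 1 − (1 − p)^60:*

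| Assumed true rate p | Expected cases (60p) | Chance of at least one |
|---|---|---|
| 0.3% | 0.18 | 16% |
| 0.5% | 0.30 | 26% |
| 1% | 0.60 | 45% |
| 2% | 1.20 | 70% |

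*Power of a formal comparison, assuming 1% against 5%, two-sided 5% level:* the pooled normal approximation gives z = (0.04 − 1.96 × √(2 × 0.03 × 0.97/30)) / √((0.01 × 0.99 + 0.05 × 0.95)/30) = −1.06, a power of about 14%. That is generous with expected counts of 0.3 and 1.5. Fisher's exact test is not significant at 0 against 5 events (p = 0.052) and needs 0 against 6 (p = 0.024). Its power, summed over all pairs of binomial counts, is about 0.2%.

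Complete recording would therefore add a descriptive count and a wide bound. It would not add a usable test.

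**The case against.** The short SAE list is deliberate and reasoned. Background life-threatening events are frequent in ICU, risk category A does not require adverse-event documentation, the investigators go beyond that requirement, and the ethics committee approved the study. The Objectives describe the adverse effects of interest as gastrointestinal symptoms, glucose and aspiration. The Discussion treats aspiration as the most severe adverse event. No section names perforation or necrosis as an effect of either regimen.

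Much of this stands. Excluding patients who already have a contraindication does not amount to saying that feeding causes it, and the exclusion has a second, practical reason. But the ICU-background argument explains why not every event is collected. It does not explain leaving out a few intestinal events that the protocol itself connects with harm from enteral feeding. Nor does it remove the conflict with the promise to monitor for any feeding-related event.

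A reader might also infer three stronger things that the documents do not support:

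- **That such an event would go entirely unrecorded and unseen by the sponsor and ethics committee.** The bedside sheet leaves open space for adverse events, and unanticipated problems must be reported. Since no severe events are expected from the formula's components after careful enrolment, a new perforation could well be judged unanticipated.
- **That the trial would report zero events in each arm.** An event with no category has no reported count, which is different from a reported zero.
- **That a valid comparison between arms is being lost.** With 30 per arm there would be none even with perfect recording.

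**Conclusion.** The point holds as a gap in defined harms collection. The SAE rule and the side-effect list together leave new non-fatal intestinal perforation, peritonitis and necrosis/ischaemia without a defined record or a count by arm. This conflicts with the general monitoring promise and fits poorly with the reason given for the exclusion criterion. The informal routes soften the gap without closing it, and the day 1–4 destruction rule weakens them further.

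The size is modest. The primary outcome is unaffected. What is lost is a descriptive safety count: at best a 9.5% one-sided upper bound from 0 of 30, with a 16% to 70% chance of seeing any case in 60 patients if the true rate lies between 0.3% and 2%. Those rates are assumed. The conclusion does not depend on them, because it follows from the text. It does assume that the case report form and safety forms, which are not shown, follow the lists in the article. The change is worth making because it is cheap.

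**What to change.** 1. Reconcile the sections Adverse event reporting and harms, Adverse events and Serious adverse events. Add new intestinal perforation, peritonitis and intestinal necrosis/ischaemia, from first study feed to closeout, to the documented SAEs, with the existing 7-day and 15-day timelines.
2. Tabulate these events descriptively by randomised arm beside aspiration and death, with exact limits and no formal test.
3. In Plans to promote participant retention, state that SAE records of withdrawn or replaced patients are kept and counted in the arm to which they were randomised, as far as consent allows. Without this, the first two steps do not secure a complete count.

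The cost is a short amendment, one added field on the SAE form and one table. The downside is a few more SAE reports, some of them for events of the underlying illness. The change concerns recording only and alters no feeding or treatment rule.
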